### **4.3 Enrollment Procedures**

#### ***4.3.1 Subject Availability and Recruitment***

Each of the up to 12 centers participating in the STAGE 1 and 2 will randomize approximately five to eight subjects. Each site in the STAGE 3 efficacy study will randomize approximately 15 subjects in 24 months. Enrollment will be closed as soon as the 600 subjects have been randomized to treatment assignment. It is anticipated that more than 600 subjects will have to be enrolled to randomize 600 subjects to treatment. The clinical trial will be advertised in local and national ALS newsletters and by letters to local neuromuscular physicians and general neurologists. Based on the increase in number of participating sites and changes in the protocol, we do not anticipate difficulty in recruitment. Each of the participating sites is an active ALS center. Should there still be a lag in accrual of subjects, we would first consider the addition of more sites, followed by lengthening the time for accrual.

#### ***4.3.2 Documentation of Screening and Eligibility***

Please refer to section 6.2.1 *Screening and Informed Consent* for details regarding screening procedures and documentation of ineligibility and nonparticipation of eligible subjects.

#### ***4.3.3 Informed Consent***

The Coordination Center must receive written confirmation of IRB approval and a copy of the IRB approved consent forms from each site prior to initiation of enrollment at that center. The site investigator or IRB and Sponsor approved designee at the site will explain the protocol and obtain informed consent from all subjects prior to initiation of any research evaluations. The site investigator will determine study eligibility as determined by the inclusion and exclusion criteria. If the study subject agrees, provides informed consent, and signs the IRB approved informed consent form, the study visits are scheduled. Informed consent will also be obtained from the caregiver, by the site investigator or IRB and Sponsor approved designee at the site, with a separate consent form specific to their participation, as they will be asked to fill out a questionnaire periodically throughout the duration of the study. One copy of the signed informed consent form will be given to the subject, and another copy may be maintained in the subject's medical record. The caregiver will receive a copy of the consent they have signed as well. The informed consent details the potential benefits of participating in the research as well as the potential risks of the experimental interventions. Copies of all informed consent forms are found in Appendix 3.

When the final dosage is chosen for the last STAGE of the trial, subjects who entered the trial in STAGE 1 will be asked to sign another consent form or an addendum to the existing consent form. This consent (or addendum) will inform them of the dosage chosen and any changes to the study for this final STAGE of the trial.

#### ***4.3.4 Randomization and Randomization Number Assignment***

Detailed information on the randomization process is found in the Coordination Center Manual of Operations. The randomization will be stratified by riluzole use and blocked by site in a manner that will allow for a balanced distribution of treated and placebo patients at each site. The randomization scheme will be independently developed by the Biostatistics Center at MGH and will indicate the treatment assignment for each subject (randomization) ID number. For each site, a randomization schedule will be provided to the pharmacy that will indicate the treatment assignment. The Randomization ID will also be used to identify the subject's Source Documents, electronic case report forms (eCRFs), laboratory tests, and all communications. The team of biostatisticians in the Biostatistics Center will develop the randomization plan and randomization sheets to be distributed to each of the research pharmacies under the guidance of the chief biostatistician. All Coordination Center clinical trial staff, with the exception of the Pharmacy Monitor, will remain blinded to all treatment assignments. Subjects, investigators, study monitors, site coordinators, and site clinical evaluators will also be blinded to treatment group assignment throughout the study. For STAGE 1 there will be an additional randomization to the time of the second lumbar puncture for CSF sampling. This randomization will be sent via the electronic data management system to the sites prior to the subject visit.

If a STAGE 1 subject who has been randomized decides to withdraw from the trial within seven days of the randomization date, the subject may be replaced. Subjects enrolled in STAGE 1 who do not successfully complete their pharmacokinetic visit will continue in the study, but will also be replaced as STAGE 1 subjects, so that complete pharmacokinetic data can be obtained on 60 subjects. Successfully completing the pharmacokinetic visit is defined as having CSF collected at the two predefined time points. In this case, the randomization parameters (treatment code, LP time for STAGE 1 subjects) will be returned to the pool of available combinations. The EDC system will be programmed to perform this procedure with manual input from the Data Manager. This replacement will not occur with STAGE 3 subjects.

## **5. STUDY INTERVENTIONS**

### **5.1 Study Drug – Interventions, Administration, and Duration**

#### ***5.1.1 Dosage***

The treatment arms in STAGES 1 and 2 are ceftriaxone 2 grams per day, ceftriaxone 4 grams (2 g bid) or placebo administered intravenously. All subjects in STAGES 1 and 2 will be instructed to take one syringe (20 ml) in am and one in pm (see Section 5.1.5). The results from the pharmacokinetic study in STAGE 1 and the safety study in STAGE 2 will guide decisions on the final dosage for the STAGE 3 study. The results from the STAGE 1 pharmacokinetic study may also necessitate an adjustment of dosage during STAGE 2. Based on review of unblinded data

by the DSMB and a few members of the Steering Committee, 4 grams/day was chosen as the dosage for STAGE 3. Since the study is an on-going adaptive design study and the current STAGE 1 and 2 subjects are included in the STAGE 3 analyses, no unblinded data will be available until the study is completed.

### ***5.1.2 Study Drug Administration***

Ceftriaxone or placebo will be administered via the single lumen catheter using an electronic pump and microbore tubing. Ceftriaxone or placebo (20 ml) is administered intravenously over 20 minutes +/- 10 minutes. The subject will receive the first dose of ceftriaxone at the site on Day 0 and will be instructed on use of pump and how to administer the study drug. Subjects will only take one dose on Day 0. They will start taking the full dosage the following day. All subsequent doses will be administered in the home by the caregiver, with the exception of the doses given at the hospital during study visits.

Prior to receiving the study drug, all subjects and caregivers will participate in training regarding care and use of central venous catheters. Training will include use of the pump, administration of study drug, drug storage and handling, catheter care, and exit site care. The subject and caregiver will be required to pass a competency assessment to demonstrate their knowledge and skills in catheter care and use. This training and competency evaluation will occur prior to catheter placement, so that the possibility of subjects receiving the catheter but not being allowed to start study drug is eliminated. Following discharge, a home visit by a visiting nurse will be available, if needed, to evaluate the exit site, catheter function and the caregiver's ability to care for the catheter and exit site. Throughout the study, trained healthcare personnel will be available to answer questions and offer ongoing instruction as needed. A training video will be provided to each subject for further training at home. Written instructions for storage, thawing, and administration of study drug, as well as for catheter care and prevention of infection, will also be provided to all subjects.

The study drug should be kept frozen and thawed to room temperature just prior to use. Syringes should not be re-frozen. If subjects do not have any adverse reactions with study drug administration, they may be able to administer the study drug over a shorter time period (10 minutes). This decision will be made by the site investigator only after a subject has been on treatment for at least three months.

In STAGEs 1 and 2, the overall rate of biliary events was 26%. This is an expected risk from Ceftriaxone. Symptoms were improved with use of Ursodiol and dosage reduction. Therefore, the study DSMB approved the use of Ursodiol (250 mg po b.i.d.) for subjects in STAGE 3 randomized to ceftriaxone. To maintain study blind, subjects randomized to placebo (MVI) will receive a placebo Ursodiol. Ursodiol and Placebo Ursodiol will be in the form of identical tablets.

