**Specific aim two (STAGE 2)** is to assess the safety and tolerability of 2 and 4 grams per day of ceftriaxone in the same subjects with ALS after a minimum of 20 weeks of daily treatment as measured by adverse events, laboratory data and ability to remain on assigned treatment. Information from STAGE 2 will be used to decide whether to continue to a phase III efficacy study (STAGE 3) and to determine the final dosage. Subjects will continue into STAGE 3.

**Specific aim three (STAGE 3)** is to determine whether chronic treatment with ceftriaxone prolongs survival free of tracheotomy or permanent assisted ventilation and slows rate of decline in function as measured by the ALSFRS-R. The final dosage of 4g (2g bid) per day, for the efficacy study was selected based on the data obtained in STAGE 1 and 2. An additional 540 subjects will be enrolled in the study in STAGE 3.

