## 2.2.2 Safety and Clinical Use of Ceftriaxone in Humans

Ceftriaxone is generally well tolerated and severe adverse events have only rarely been reported. Over 100 million people have received ceftriaxone for the treatment of a variety of infections. Few patients have received ceftriaxone for more than six weeks. Ceftriaxone is not approved by the Food and Drug Administration (FDA) for treatment longer than 4-6 weeks. Toxicities of ceftriaxone are similar to those reported with other cephalosporins and include pseudomembranous colitis, super-infections, local pain on administration, phlebitis, fever,

pruritis, rashes, anorexia, nausea, vomiting, diarrhea, and abdominal pain. There is no evidence of teratogenicity in rodent study or in primates. There are no adequate studies in pregnant women.

Across many studies, the most frequently observed adverse events during treatment with ceftriaxone are hematological, including eosinophilia (6%), thrombocytosis (5.1%), leukopenia (2.1%), and thrombocytopenia (1%); however these adverse reactions have been reversed when drug administration was stopped [103]. Gastrointestinal adverse events during ceftriaxone therapy, primarily diarrhea (2.7%), are common. Ceftriaxone is also excreted via the bile leading to high biliary concentrations of the drug. Biliary adverse effects include the formation of biliary sludge leading to biliary obstruction, cholecystitis, choledocholithiasis, and pseudolithiasis. Prolonged use of ceftriaxone may result in overgrowth of nonsusceptible organisms. Neutropenia has been reported with ceftriaxone use. In one series, the mean time to develop neutropenia was 21 days (range 8-25 days). It was reversible upon discontinuation of the medication. The frequency of hypersensitivity skin reactions to ceftriaxone is between 1 and 3%; anaphylaxis is rare. The risk of anaphylaxis may be increased with a history of allergy to penicillin and is certainly increased with a history of allergic reaction to cephalosporin. Ceftriaxone is contraindicated in patients with known hypersensitivity to penicillins or cephalosporins. Nonconvulsive status epilepticus has been rarely reported with ceftriaxone use and is more common in patients with renal failure [104].

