### ***5.1.3 Dosing Schedule***

The first dose of study drug for each subject will be administered in the clinic and the subject will be observed for at least three hours to assess for any immediate hypersensitivity reaction.

The day that a subject starts treatment with study drug will be designated as DAY 0. All visits must be scheduled from Day 0, not the last assessment. The subjects in STAGE 1 will be randomized (1:1:1) into one of three cohorts; 2 grams ceftriaxone q day, 2 grams ceftriaxone bid, or placebo. Each subject will receive study drug twice a day. The subjects will receive two containers of syringes labeled Container A (or “a.m.”) and Container B (or “p.m.”) filled with study drug. Caregivers will be instructed to administer to the subject the contents of one syringe from Container A in the morning and one from Container B in the evening as follows for STAGE 1:

|                 | Container |          |
|-----------------|------------------|----------|
| Group    | A         | B |
| 2 grams per day | X                | 0        |
| 4 grams per day | X                | X        |
| Placebo         | 0                | 0        |

("0" = Placebo, "X" = ceftriaxone 2 grams)

|                                   | AM | PM |
|-----------------------------------|-----------|-----------|
| Day 0 – STAGE 2 conclusion | A         | B         |

**STAGE 3:** The final dosage for STAGE 3 will be 4 g (2 g bid). Study drug will be administered twice daily, once in the morning and once in the evening.

Subjects will receive the study drug until the last enrolled subject completes 52 weeks of treatment.

Subjects will also be instructed to take one tablet (Ursodiol or Ursodiol Placebo) twice daily (AM and PM) with food while on study drug (Ceftriaxone or Placebo).

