### **7.2 Adverse Experiences Related to Ursodiol**

Ursodiol is FDA approved for the chemodissolution of bile duct stones, gallstones, prophylaxis of gallstones during rapid weight loss and primary biliary cirrhosis. Contraindications include hypersensitivity to bile acids or ursodiol. Adverse events occurring more frequently with ursodiol than placebo include diarrhea (1.3%), elevated creatinine (1.3%), elevated blood glucose (1.2-1.3%), leukopenia (2.6%), peptic ulcer (1.3%) and skin rash (2.6%)[180].

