### *Analysis of Secondary Outcome Variables*

**Safety and Tolerability.** The safety data will be summarized by treatment group. The treatment groups will be compared with respect to occurrence of each adverse event. Total number of adverse events and abnormal laboratory tests will be compared between groups using Fisher's exact test. Withdrawal, abnormal laboratory tests, vital signs and use of concomitant medications will be assessed to characterize the safety profile of ceftriaxone. Compliance data will be determined for each visit and by treatment group. The time to subject refusal will be compared between treatment groups in order to better determine tolerability. This will be accomplished using a method of survival analysis that allows informative censoring due to death [188]. Descriptive statistics denoting the changes from baseline to the final assessment visit with respect to key laboratory parameters and vital signs will also be provided.

**VC, Dynamometry and Quality of Life.** Our primary analysis strategy is to use a random effects analysis of variance using PROC MIXED in SAS [189]. The basic idea of this model is that each subject has his or her own trajectory with a random, slope, intercept and curvature the average value of which may depend on treatment. Since the subject groups start out the same, the intercept will not depend on treatment but the slope and curvature may. In our trial of topiramate this model was sensitive to a negative effect on muscle strength on treatment.

There was a significant curvature but only the slope was affected by treatment. The advantage of using this model is that it accommodates the variable duration of follow-up that will result from our trial design. We will look carefully at the residuals for this model to be sure that it fits the data. If there appear to be problems with fit, we will use a robust approach of assessing significance where the p-value for any treatment contrast is calculated using a permutation test.

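### Stage 3 compares ceftriaxone with ursodiol against double placebo, but Aim 3 and the safety analysis credit the results to ceftriaxone

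*Combined protocol and SAP*

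**What the plan says.** Section 5.1.2 explains that biliary events in Stages 1 and 2 led to a second drug: "the study DSMB approved the use of Ursodiol (250 mg po b.i.d.) for subjects in STAGE 3 randomized to ceftriaxone". To protect the blind, "subjects randomized to placebo (MVI) will receive a placebo Ursodiol". Section 5.1.3 continues the tablet twice daily for as long as the infusion is taken. Stage 3 has only these two arms.

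The stated question was not changed to match. Aim 3 (section 1.1) is "to determine whether chronic treatment with ceftriaxone prolongs survival free of tracheotomy or permanent assisted ventilation" and slows functional decline. Section 9.1.3 opens by posing survival and ALSFRS-R as two separate questions about ceftriaxone. Its safety paragraph, under Analysis of Secondary Outcome Variables, compares the treatment groups on each adverse event and uses withdrawals, laboratory results and vital signs "to characterize the safety profile of ceftriaxone". Ursodiol appears in section 9 only in the monitoring text, which schedules a safety review three months into Stage 3.

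**The concern.** The randomized contrast differs from the one named in the aim and the analysis. Each subject in the active arm is assigned both drugs and each control is assigned neither, so no comparison within Stage 3 separates them.

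For survival and ALSFRS-R, a difference between the arms belongs to the regimen. Crediting it to ceftriaxone requires ursodiol to have no effect on either endpoint, and the plan does not state that assumption.

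For safety, sections 2.2.2 and 7.2 list some of the same events for both drugs. Followed as written, the analysis would report leukopenia and rash to which ursodiol contributed as part of ceftriaxone's profile. It would also report a biliary rate modified by a drug added to manage biliary events. Those figures could then be read as the risk of ceftriaxone itself.

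**Working it through.** **1. What each Stage 3 arm receives (sections 5.1.2 and 5.1.3).**

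| | Active arm | Control arm |
|---|---|---|
| Infusion | ceftriaxone, 4 g/day | multivitamin placebo |
| Tablet | ursodiol, 250 mg twice daily | ursodiol placebo |

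**2. The plan's own power figure.** Section 9.1.3 claims over 80% power with 600 subjects for a 50% longer median, a hazard ratio of 1.5 (placebo over active). Allocation is 40 + 360 = 400 active and 20 + 180 = 200 placebo, so p = 1/3. Using power = Φ(√(E·p(1−p))·ln 1.5 − 1.96):

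- E = 243 events (alternative): √(243 × 2/9) = 7.35; 7.35 × 0.405 − 1.96 ≈ 1.02; power 84.6%.
- E = 293 events (null): power 90.5%.

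The claim reproduces. It is power for whatever separates the arms, that is, for the regimen.

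**3. Efficacy attribution.** If effects multiply, ceftriaxone's hazard ratio is 1.5 divided by ursodiol's. The documents give no value for ursodiol, so the range below is an assumption.

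| Ursodiol hazard ratio (assumed) | 1.0 | 1.1 | 1.2 | 1.3 |
|---|---|---|---|---|
| Implied ceftriaxone hazard ratio | 1.50 | 1.36 | 1.25 | 1.15 |

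Reading the result as ceftriaxone's takes the first column without saying so.

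**4. Overlapping harms.** The ursodiol rates u come from section 7.2 and the ceftriaxone rates c from section 2.2.2. Share from ursodiol = u/(c + u), assuming that the rates add and that u is an excess over about zero. Expected counts use 400 active subjects, the number randomized. Roll-over subjects lost before Stage 3 would lower them.

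| Event | c | u | Ursodiol share | Expected of 400: ceftriaxone + ursodiol |
|---|---|---|---|---|
| Leukopenia | 2.1% | 2.6% | 2.6/4.7 = 55% | 8.4 + 10.4 |
| Skin, low c | 1% | 2.6% | 2.6/3.6 = 72% | 4 + 10.4 |
| Skin, high c | 3% | 2.6% | 2.6/5.6 = 46% | 12 + 10.4 |
| Diarrhea, general rate | 2.7% | 1.3% | 1.3/4.0 = 33% | 10.8 + 5.2 |
| Diarrhea, 2 g/day in the Lyme report | 10% | 1.3% | 1.3/11.3 = 12% | 40 + 5.2 |
| Diarrhea, 4 g/day in the Lyme report | 50% | 1.3% | 1.3/51.3 = 2.5% | 200 + 5.2 |

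The Lyme disease report in section 2.2.2 puts mild to moderate diarrhea at about half of patients on 4 g/day, the Stage 3 dosage. If that figure applies, the diarrhea overlap is small. Section 7.2 also lists raised creatinine at 1.3% for ursodiol. Sections 2.2.2 and 7.1 give no matching ceftriaxone percentage, so no share can be computed.

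**5. Biliary events.** Sections 2.2.2 and 5.1.2 give 26% for Stages 1 and 2 and say that ursodiol helped. Routine ursodiol would be expected to move the Stage 3 rate the other way, downward. The size cannot be computed. The denominator of the 26% is not stated, section 2.2.2 calls the events symptomatic while section 5.1.2 does not, and ursodiol was already used to manage events in those stages.

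**The case against.** The strongest reply is that the documents say ceftriaxone and nowhere claim to study it without supportive treatment. Section 5.1.2 openly explains why ursodiol was added, and the placebo tablet keeps the comparison blinded and fair. This stands. A reader might infer that Stage 3 cannot answer its question because it does not test ceftriaxone alone. The documents do not support that: the word *alone* is not theirs, and nothing in them indicates that ursodiol alters ALS.

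A second reply is that the rates are poorly matched. Section 2.2.2 says few patients have had ceftriaxone beyond six weeks, whereas Stage 3 follow-up runs 12 to 36 months. Short-term figures can transfer badly: section 7.1 puts biliary sludge and cholelithiasis each below 0.1% short-term, against 26% for biliary events in Stages 1 and 2. Hypersensitivity skin reactions are also not the same category as skin rash. This stands too, so the shares show only that the overlap is not negligible. The one-third share for diarrhea should not be relied on.

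A third reply is that provisions exist: the month-3 review of ursodiol safety, separate tablet counts (section 5.2.3), a separate list of ursodiol events (section 7.2), and the Stage 1 and 2 finding that ursodiol was well tolerated and left ceftriaxone blood levels unchanged. These help monitoring but do not separate the drugs. The review sees the same confounded arms, and unchanged levels exclude one interaction, not an independent ursodiol effect.

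A reader might also take Stages 1 and 2 as a clean ceftriaxone-only comparison. They are not, because some subjects received ursodiol for biliary events.

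**Conclusion.** The point holds as a mismatch between the regimen tested and the drug named. The design and the primary tests remain valid for ceftriaxone with ursodiol against double placebo.

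For efficacy it is a limit on attribution: a ceftriaxone-only claim rests on an unstated assumption that ursodiol affects neither survival nor ALSFRS-R. No bias has been shown.

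For safety it is concrete. Adverse event rates from Stage 3, or pooled over Stages 1 to 3, are not ceftriaxone-specific for leukopenia, rash and biliary events, and possibly not for creatinine. For diarrhea the effect is probably small at the Stage 3 dosage. The shares of 55% and 46% to 72% depend on additivity and on short-term rates, so they should be read as scale and not as predictions.

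**What to change.** In Aim 3, section 9.1.3 and its safety paragraph, name the Stage 3 treatment as ceftriaxone with ursodiol and the comparator as matching double placebo. State that any ceftriaxone-only efficacy claim assumes ursodiol has no effect on survival or ALSFRS-R.

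In the safety summary, report biliary, leukopenia, rash, diarrhea and creatinine events in two parts:

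- the Stage 1 and 2 cohort up to each subject's first ursodiol use, by dose arm and placebo;
- the period on both drugs, against double placebo.

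The cost is wording and one extra table from data already collected. The claim becomes narrower, and the earlier-period table will be imprecise, with about 40 active subjects on two doses and some follow-up cut short at ursodiol use. Separate causality ratings for the two drugs are not proposed, because a blinded investigator could rarely divide an event between drugs taken together. No change to who receives ursodiol is proposed.
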